## Abstract

**Background:**

Borderline personality disorder (BPD) is one of the most frequent, most debilitating and lethal mental conditions and is associated with a serious burden of disease. Treatment for patients with BPD involves structured psychotherapy, and may involve brief psychiatric treatment as first-line intervention. No controlled study has assessed the effectiveness of such brief intervention. Whereas most psychotherapy studies in patients with BPD focus on the effectiveness of the intervention, we still lack an understanding of how and why these effects are produced from a patient process perspective. It is therefore of utmost importance to study the treatment-underlying *mechanisms of change*. The present study plans to apply novel measurement methods for assessing change in two central psychobiological processes in BPD: emotion and socio-cognitive processing. The study uses theory-driven and ecologically valid experimental tasks, which take the patient’s individual experience as the anchor, by integrating methodology from psychotherapy process and neurofunctional imagery research.

**Methods:**

The aim of this two-arm, randomized controlled study is to test the effects (i.e., symptom reduction) and the underlying mechanisms of change associated with a brief psychiatric treatment (10 sessions over 4 months), compared with treatment as usual. Participants (*N* = 80 patients with BPD) undergo assessments at four points (intake, 2 months, discharge, and 12-month follow up). In addition to symptom measures, individuals undergo a 2-step assessment for the potential mechanisms of change (i.e., emotion and socio-cognitive processing): (1) behavioral and (2) (for a sub-sample) neurofunctional. We hypothesize that change in the mechanisms explains the treatment effects.

**Discussion:**

This study uses an easy-to-implement treatment of BPD, and a sophisticated assessment procedure to demonstrate the critical role of psychobiological change in emotion and socio-cognitive processing in brief treatments. It will help increase the effectiveness of brief treatment for BPD and help diminish the societal burden of disease related to BPD, in these early stages of treatment.

**Trial registration {2}:**

ClinicalTrials.gov: NCT03717818. Registered on 24 October 2018). Protocol version {3} number 2 from 9 February 2018.

## Background and rationale {6a}

Borderline personality disorder (BPD) is one of the most prevalent mental disorders with a prevalence of 2–3% in the general population. Direct societal costs are related to frequent use of emergency services, intense use of inpatient and outpatient treatments, indirect societal costs stemming from prolonged sick leave, abusive consumption of street-drugs, intra-familiar abuse and neglect and in some cases legal costs [1, 2].

Psychological treatments are considered first line for problems related to personality disorders [3–6]. Although there are several theoretical accounts on how these effects are produced, there is a paucity of systematic empirical research focusing on mechanisms of change in treatments of personality disorders (PDs) [7–13], aiming at *empirically explaining* how treatments work and, ultimately, *increasing* the treatment’s effectiveness. Such an empirical understanding would be particularly useful at the beginning of treatment: a better knowledge of the determinants of initial symptom alleviation in psychological treatment would allow us to deliver even more potent treatments for these patients from the very first session on, and to prevent some of the long-term consequences of the disorder.

The objective of the present study is to explain early symptom change in patients with borderline personality disorder undergoing a brief psychiatric treatment that is consistent with the international and national treatment guidelines [3, 14]. We assume that symptom change is the result of a complex interplay between changing central process characteristics of the patient - assessed from an integrated neuro-behavioral perspective - and the moment-by-moment responsive adjustment to them by the therapist. The present trial examines two patient-related mechanisms of change in treatments of BPD: (1) emotion processing and (2) change in socio-cognitive processing. Aimed at discovering the underlying “laws of change” in patients undergoing brief treatments for BPD, such research may help increase the effectiveness of any bona fide therapy approach from the very first session on and thus may help decrease direct and indirect societal costs related to BPD.

In order to achieve this, we aim to study a specific brief guideline-based intervention for BPD. In addition to the structured psychotherapy models validated for the treatment of BPD (e.g., dialectical-behavior therapy (DBT), mentalization-based therapy (MBT), transference-focused psychotherapy), the past 10 years have witnessed the emergence of psychiatric approaches to the treatment of BPD [15, 16]. In a randomized controlled trial, McMain and colleagues [17, 18] have tested the efficacy of a 1-year-long dialectical-behavior treatment program compared to a general psychiatric management (GPM) program, also lasting 1 year [19, 20]. The results were somewhat unexpected, showing that both treatments performed equally well on all outcome indices and most process characteristics, including symptom relief up to 2 years after the end of treatment. Bateman and Fonagy (2009) used a similar type of psychiatric approach in which they found consistent results with regard to the comparison with MBT [21]. These emerging studies may suggest that for at least the first phase of treatment of patients with BPD, it might be sufficient to offer a psychiatric intervention that is easily learnable; as such, we increase general access to mental health intervention for a large amount of patients with BPD [22, 23]. Such new healthcare models have been advocated within the literature on stepped care for BPD [24–26].

To date, no study has examined such a brief guideline-based psychiatric intervention, together with its explanatory mechanisms of change for outcome, compared to treatment as usual. This is the aim of the present research. It will determine the effectiveness of a brief psychiatric intervention and detail its psychobiological underpinnings of change.

### A methodological problem and a possible solution

Earlier studies focusing on mechanisms of change in treatments for BPD fall into two major categories, neglecting a possible methodological integration explaining psychobiological change. Some studies have involved psychotherapy process research, describing change on central patient variables in-session [27–29] favoring external clinical validity, but remaining sensitive to the session-internal influences by the patient-therapist interaction (i.e., therapist responsiveness) [30]. Other studies have involved biological assessments of change where the changing variable was observed on neurobiological activation to the exposed standardized stimuli [31, 32] - favoring internal validity, but neglecting the idiographic content so central to understanding change in psychotherapy.

In order to address these methodological problems, we suggest researchers should carefully integrate methods from psychotherapy process research with neurofunctional methods, by taking into account the *individual’s subjective experience* as the anchor - substantiated in the form of *individualized* stimuli in the experiment - in the assessment of the mechanisms [12, 33]. This is only meaningful when the design controls for a number of manipulation checks (see “Methods”). Such an integrated experimental design goes beyond the systematic assessment of the therapy process, as described by our earlier studies [28, 34, 35]; in addition, it becomes possible to relate aspects of the patient’s subjective experience to the neurobehavioral correlates of change (see also the discussion by Tashiro et al., 2006, and [name], 2019 [12, 36]).

### Mechanisms of change in treatments for borderline personality disorder

Here, we subsequently focus on two potential mechanisms of change that are among the most potent so far, and embed them within our integrative conception of mechanisms of change: (1) emotion processing and (2) socio-cognitive processing.

### Emotion processing: change in affect-meaning states related to self-criticism

Change in emotion processing is central for psychotherapy in patients with BPD [37]. Greenberg and colleague (2006) have differentiated between, among others, emotion regulation and emotion transformation [38]. With regard to emotion regulation over the course of psychotherapy, Neacsiu and colleagues (2010) showed that the acquisition of specific coping-skills strategies, aiming at more efficient emotion regulation, functioned as a mediator of change in DBT [39]. These findings are in line with the results of a pilot functional magnetic resonance imaging (fMRI) study: Schnell and Herpetz (2007) investigated cognitive reappraisal over the course of inpatient DBT in six patients with BPD [31]. The authors identified a decrease in activation over the course of therapy at the levels of the right anterior cingulate cortex (ACC), the temporal and posterior cingulated cortex and the left insula [31]. Using a previously validated procedure of cognitive reappraisal [40], Schmitt and colleagues (2016) partially confirmed these results in a sample of patients with BPD (*N* = 32 patients) undergoing DBT and identified enhanced neural connectivity between ventro-lateral pre-frontal cortex areas and the amygdala [32], consistent with the neuropathological model put forward by New and colleagues (2007) [41]. Comparable results were obtained in 11 patients with BPD undergoing DBT, compared with 11 healthy controls: decreased amygdalar reactivity was identified after DBT [42, 43]. Consistent results were identified for change in distraction as a strategy for regulation of emotion [44] and change in pain-mediated regulation of emotion [45]. Perez and colleagues (2015) identified consistent effects in favor of enhanced fronto-limbic connectivity after 1-year long transference-focused psychotherapy (TFP) in 10 patients with BPD [46]. Taken together, these results suggest improved emotion regulation capacities after therapy in patients with BPD, but more research integrated within a larger theoretical framework is needed.

In addition to the regulation perspective on emotion, we define *emotion transformation* as the change process by which emotions unfold and change over time from the least productive to the most productive, the latter being underpinned by increased meaning-making [47]. It was shown that this process relates to healthy functioning and a good outcome from psychotherapy [34], in particular the flexibility of emotional experiences [47]. The relevance of this dynamic conception of emotion processing to BPD was supported in terms of change in anger processing [48] and in terms of change in undifferentiated global distress [27]. It was shown to also be of relevance in narcissistic and histrionic PDs [49, 50].

This transformation conception may explain the resolution of harsh self-criticism, a central clinical feature of BPD [48, 51–53]. Whelton and Greenberg (2005) proposed a paradigm of studying emotion transformation related to self-criticism using the empty-chair dialogue. Patients criticized themselves in a structured assessment procedure using imaginative and emotion-eliciting enactment tasks. It appeared that the depressive persons presented more self-contemptuousness in their self-criticism, compared to controls and presented with higher levels of shame, sadness and emotional collapse, along with less pride [54]. This study was on 45 undergraduates presenting with or without anger problems, using the same paradigm [49]. What differentiated the two groups was the presence of self-contemptuousness, *t* (1, 43) = 1.91, *p* < .05) associated with the self-criticism, along with the absence of the existential need in the anger-prone individuals. This means that for anger-prone participants - who share this clinical feature to some extent with BPD - self-criticism is particularly harmful to the emotion transformation when associated with self-contemptuousness. We may therefore assume that decrease in self-contemptuousness - and possibly increase in its antidote, self-compassion - and increase in emotion flexibility are markers of productive change in treatment.

Emotion transformation related to self-criticism is underpinned by biological changes. Using standardized stimuli, Longe et al. (2010) showed in a female student sample (*N* = 17) a blood oxygen level dependent (BOLD) activation (intra-subject comparison to a neutral condition at the level *p* < .05 corrected) in the left pre-frontal cortex (PFC; Brodman area (BA) 45), in the lateral orbito-frontal cortex (OFC; BA 47), in the left dorsolateral PFC (BA 9) and in the inferior and middle temporal gyrus (BA 20 and 21, including the lingual gyrus, BA 19) [55]. The hyperactivity in pre-orbito-frontal and orbito-frontal regions associated with self-criticism in this study was interpreted as linked with the inhibitory behavior known to be associated with activation of the lateral PFC [56]. Brain activity in the striatum has been associated with self-punishing emotions of self-criticism [54], such as shame, anger about the self and self-contemptuousness [35]. In addition, some regions of the insula-basal ganglia networks are known to be associated with processing of disgust [57]. In an fMRI study using *individualized* self-critical stimuli (which were previously selected based on a large set of words), Doerig and colleagues (2013) showed bilateral insula activation, along with activations in left hippocampus and amygdalar formations, interpreted as regions recruited in emotion processing of self-critical stimuli [58]. More research is needed to understand change in self-contemptuousness and its neuronal substrates over the course of treatment for BPD, when an individualized measurement method is applied.

### Change in socio-cognitive processing: integrating “hot” interpersonal information

Change in the patient’s *socio-cognitive or mentalizing capacities* is discussed as a putative mechanism of change in the treatment of BPD [52, 59, 60]. Levy and colleagues (2006) examined change in three forms of psychotherapy for BPD -– TFP, DBT and supportive therapy - and found that only TFP was associated with an increase in mentalizing functions, along with development of more secure attachment patterns in some patients in this group [29]. Consistent results were presented by Fischer-Kern and colleagues [61] (see also de Meulemeester et al. [62]; Maillard et al., [63]). Other research has underlined the moderating factor of mentalizing capacities for outcome for different categories of PD [64, 65]. To our knowledge, no studies have shown mediation for changes in socio-cognitive processing in treatments for BPD.

One method to investigate the core interpersonal contents related with attachment figures (i.e., “hot” stimuli), again formulated from an *individualized* perspective, is the core conflictual relationship theme (CCRT [66]). A CCRT is a formulation composed by a patient’s wish (e.g., to be close, to be treated harshly), the anticipated response of the other/the object (e.g., to facilitate one’s independence, to be harsh) and the response of the self (e.g., to feel understood, to be frustrated). According to Luborsky (1998), the *pervasiveness* of a CCRT is the degree of generality of a theme across specific relationship episodes and specific interactions [66]. In patients with BPD, one may identify a central theme for each person, which is present in more than 60% of the specific relationship episodes [67, 68]. After treatment, it is expected that pervasiveness related to the core theme decreases. Luborsky (1998) demonstrated in 33 patients undergoing psychodynamic psychotherapy - although not patients with BPD - a pre-post decrease in pervasiveness over time (*F* (1, 32) = 7.4, *p* < .01), which was particularly strong for the category of the negative response of the self. This decrease correlated with symptom change at the end of treatment [66]. Therapy studies in patients with BPD are needed, to test the role of decrease in CCRT pervasiveness over time.

As such, an emerging field of research focuses on the explanatory roles of (1) the patient’s emotion processing and (2) the patient’s capacities of socio-cognitive processing, for treatment effects related to PDs. We think that the most promising assessments rely on integration between idiographic and nomothetic assessment procedures.

### Objectives {7}

(1) Outcome: a 10-session BPD-specific guideline-based treatment produces more reduction in specific borderline symptoms than non-specific treatment as usual (TAU). (2) Global change: a 10-session BPD-specific treatment presents pre-post change in socio-cognitive processing (SCP) and emotion processing (EP), which is not the case in the TAU. (3) Treatment response: SCP and EP change more in treatment responders, compared to non-responders (across conditions). (4) Mediation: the changes in these potential mechanisms of change will function as mediators of symptom decrease (between intake, discharge and follow up; the latter will be used to disentangle potential time confounds). Change is operationalized on behavioral and neurofunctional (by controlling for the corresponding behavioral/idiographic information) levels. For post-therapy EP, we expect greater emotional variability when dealing with individualized self-criticism, along with lesser self-contemptuousness, compared with pre-therapy. It is expected that post-therapy neuronal activations are lower in a EP network involving areas in the PFC, the striatum and the insula-basal ganglia [57, 58], when compared with pre-therapy. For post-therapy SCP, we expect lower CCRT pervasiveness, when compared with pre-therapy and we expect that post-therapy neurofunctional activations are lower in regions associated with the theory of mind (i.e., anterior cingulate, precuneus, inferior and middle frontal gyri and inferior parietal lobes) [69–71], compared with pre-therapy.

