### Outcomes {12}

The main outcome measure is the Zanarini Rating Scale for Borderline Personality Disorder (ZAN-BPD) [76]. The ZAN-BPD is a continuous hetero-administered measure assessing the nine criteria outlined in DSM-5, on a continuous Likert-type scale ranging from 0 to 4. As such, it yields a total theoretical score of 36. A comprehensive validation study has shown its reliability, validity and sensitivity to change [76].

Emotion processing related to self-criticism will be assessed using the self-criticism task. This task involves two main steps: (1) conduct of a two-chair dialogue on self-criticism, an individualized and therefore particularly emotion-arousing procedure [35, 54, 77] and observer’s process rating of the patient’s emotions using the Classification of Affective Meaning States (CAMS) [78] (see also [34, 47]) with the aim of extracting 20 individualized self-critical words for each patient at each assessment point. Increase in emotion flexibility (i.e., more different emotion categories as a reaction to the self-criticism) over time, along with a decrease in self-contemptuousness associated with the self-criticism over time, are indicators of productive change; (2) 1 week later, a test of neural correlates of the processing related to the 20 individualized self-critical words (extracted from step 1), in comparison with a set of 20 negative emotional [79], 20 positive emotional [79]), 20 neutral words and 20 non-words (symbols; in total 100 words; presented in a random order). Self-reported emotional arousal (on a self-assessment manikin (SAM)) and self-esteem (on the State Self-Esteem Scale (SSES)), along with observer-reported fear/shame (on the CAMS) reaction, will be measured as manipulation checks for step 1; SAM assessment will be performed for each stimulus presented in the scanner. This task was empirically tested in a non-published pilot study: in 5 individuals, we showed higher subjective arousal levels for the individualized words than for the standardized negative words, along with comparable neurofunctional activations.

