## Statistical methods

### Statistical methods for primary and secondary outcomes{20a}

For the behavioral assessments and all outcomes, we will conduct intent-to-treat and completer analyses for all variables (hypothesis 1: outcome, defined as residual gains at discharge). We will use multilevel modeling [103] where appropriate, for hypotheses 2 and 3 (global change and treatment response). For hypothesis 4 (mediation), we will conduct a mediation analysis for both potential mechanisms of change [104]. Raw and composite scores for outcome and all mechanisms of change indexes will be used, by controlling for the corresponding fMRI data from the same assessment point. Composite scores for EP involve combining pre-post change in contemptuousness with change in neuronal regions of interest for individualized self-criticism. For SCP, this involves combining pre-post change in CCRT pervasiveness with change in neuronal regions of interest for theory of mind.

We will control for therapist effects in the three-level hierarchical linear modeling (HLM) [105]. All indexes (i.e., behavioral and fMRI) in the patient groups (*N* = 80) at intake will be rigorously compared with the indexes found in the healthy control group (*N* = 20); we expect systematic between-group differences, in the context of a control analysis. Statistical treatment packages HLM7 and SPSS23 will be used for the analyses of the behavioral indexes.

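### Hypothesis 3 compares responders with non-responders although the symptom outcomes are continuous; testing it on continuous symptom change would recover information at almost no cost.

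*Protocol article*

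**What the plan says.** Objectives {7} of the protocol article gives the third hypothesis as "Treatment response: SCP and EP change more in treatment responders, compared to non-responders (across conditions". Statistical methods {20a} assigns it, with hypothesis 2, to a model class: "We will use multilevel modeling [103] where appropriate, for hypotheses 2 and 3 (global change and treatment response". No responder variable, instrument, threshold or time point is given in either place.

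Elsewhere the symptom outcomes stay continuous:

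- Outcomes {12}: "The main outcome measure is the Zanarini Rating Scale for Borderline Personality Disorder (ZAN-BPD". Its nine criteria are each scored "on a continuous Likert-type scale ranging from 0 to 4", for a maximum total of 36.
- Statistical methods {20a}: "hypothesis 1: outcome, defined as residual gains at discharge".
- Objectives {7}, hypothesis 4: "the changes in these potential mechanisms of change will function as mediators of symptom decrease".
- Statistical methods {20a}, in the text following the mediation analysis: "Raw and composite scores for outcome and all mechanisms of change indexes will be used".
- Statistical methods {20a}, fMRI paragraph: the outcomes enter the group-level models as regressors, without a split.

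**The concern.** Hypothesis 3 asks whether patients whose emotion processing (EP) and socio-cognitive processing (SCP) change more are also those whose symptoms improve more, whichever arm they were in. A responder grouping answers this with a coarsened version of the symptom change: patients just either side of the line count as different, and all patients on one side count as the same. The finer score will already be in the data set.

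The trial recruits 80 patients and allows for 30% dropout, so there is little information to spare. If hypothesis 3 gave a null result, a reader could not tell whether the mechanism and the symptoms are unrelated or whether the grouping hid a real link. The result would also depend partly on where the line falls.

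**Working it through.** **Plan's own figure.** There is none for hypothesis 3. The power of 0.819 in Sample size {14} is given for two concomitant mechanisms with d = 0.60 and is not tied to a responder contrast, so there is nothing to reproduce for this point.

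**Inputs**

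- From Sample size {14}: N = 80; 30% dropout, so 80 × 0.70 = 56; two-tailed alpha 0.05; d = 0.60.
- Assumed: responder share p of 50%, 30% or 20%, because the article gives none.
- Assumed: mechanism change and symptom change are bivariate normal.
- Assumed for step 2 only: d = 0.60 is the responder versus non-responder difference in mechanism change.

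**Step 1. Information lost by splitting.** With q = 1 − p and φ(z) the standard normal density at the cut, the efficiency of the split relative to the continuous score is φ(z)² / (pq).

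| p | φ(z)² | pq | Efficiency | Loss | 80 patients act like |
|---|---|---|---|---|---|
| 0.50 | 0.1592 | 0.25 | 0.637 | 36% | 51 |
| 0.30 | 0.1209 | 0.21 | 0.576 | 42% | 46 |
| 0.20 | 0.0784 | 0.16 | 0.490 | 51% | 39 |

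This step does not use d.

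**Step 2. Power if d = 0.60 is the responder contrast.** The point-biserial correlation is d / √(d² + 1/(pq)). The underlying correlation is r = r_pb × √(pq) / φ(z). At p = 0.50: r_pb = 0.60 / √(0.36 + 4) = 0.287, and r = 0.287 × 0.5 / 0.399 = 0.36. The other shares give r = 0.35 and 0.33. Simulated power, two-sample t test at the cut against the test of the continuous correlation:

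| p | r | N | Split | Continuous | Loss (points) |
|---|---|---|---|---|---|
| 0.50 | 0.36 | 80 | 0.75 | 0.91 | 16 |
| 0.30 | 0.35 | 80 | 0.68 | 0.90 | 22 |
| 0.20 | 0.33 | 80 | 0.55 | 0.86 | 31 |
| 0.50 | 0.36 | 56 | 0.59 | 0.79 | 20 |
| 0.30 | 0.35 | 56 | 0.51 | 0.77 | 26 |
| 0.20 | 0.33 | 56 | 0.41 | 0.72 | 31 |

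Noncentral-t power for the split agrees: 0.755, 0.680 and 0.564 at N = 80; 0.597, 0.524 and 0.422 at N = 56.

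**Step 3. Other correlations.** Holding d fixed makes the assumed r shift with the cut, so the comparison was repeated with r held fixed. Power comes from Fisher's z, with r multiplied by the square root of the efficiency for the split.

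| r | N | Continuous | Split at p = 0.50, 0.30, 0.20 | Loss (points) |
|---|---|---|---|---|
| 0.2 | 56 | 0.314 | 0.215, 0.199, 0.175 | 9.9 to 13.9 |
| 0.3 | 80 | 0.775 | 0.572, 0.529, 0.464 | 20.3 to 31.1 |
| 0.371 | 56 | 0.810 | 0.604, 0.559, 0.491 | 20.6 to 32.0 |
| 0.5 | 80 | 0.998 | 0.960, 0.939, 0.894 | 3.8 to 10.4 |

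The loss is small where the test is weak anyway or nearly certain to succeed, and largest in between. Over these cases it runs from about 4 to 32 points.

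**The case against.** The strongest reply is that a one-line hypothesis is being read as a fixed analysis. The analysis section names only multilevel modelling for hypotheses 2 and 3, no stated model contains a responder indicator, and how response is defined may sit in a fuller document. That is fair, and the missing definition is not held against the article. But the hypothesis itself is worded as a two-group contrast, and any later definition that yields two groups loses information in the same way.

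Three stronger readings are tempting, and the article supports none of them.

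- A reader might infer that the plan cuts ZAN-BPD change at a threshold. No section says so. OQ-45 and BSL-23 are also listed as outcomes, and residual gains are tied to hypothesis 1 only. ZAN-BPD is a presumption based on its role as main outcome; the argument is the same for the other scores.
- A reader might infer that the trial discards the continuous link between mechanism and outcome. It does not. Hypothesis 4 concerns symptom decrease, and the fMRI group models use the outcomes as regressors. Still, neither replaces hypothesis 3: mediation also depends on treatment shifting the mechanism, and the fMRI part covers only a sub-group.
- A reader might take 16 to 31 points as a property of this trial. It rests on applying d = 0.60 to a contrast for which the article does not state it. The pilot section says hypothesis 3 was not tested there. The calculations also use a t test and a simple correlation in place of the multilevel model.

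**Conclusion.** The point holds, within limits. Hypothesis 3 is framed as a split of patients while the symptom outcomes are continuous, and a continuous test would use more of the same data. The information loss is about 36% at an assumed 50% responder share and 51% at an assumed 20%, under bivariate normality. The power loss is 16 to 31 points only if d = 0.60 is taken as the responder contrast with N = 56 to 80; otherwise it may be anywhere from about 4 to 32 points. The basis of response is not stated. The loss is confined to hypothesis 3, which is not the primary comparison, so this is a cheap improvement and not a flaw in the trial's main result.

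**What to change.** Restate hypothesis 3 along these lines: greater change in EP and SCP is associated with greater symptom reduction, across conditions. As its main analysis, relate EP and SCP change to continuous symptom change in the planned multilevel model, using either the discharge ZAN-BPD score adjusted for intake or the residual gain from hypothesis 1. Keep responders versus non-responders as a descriptive display, and name the instrument and threshold used for it.

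The cost is about one sentence in the objectives and one in the statistical methods, with no new patients, visits or measurements. There is a small downside: the result is a slope and not a group contrast, and it assumes an approximately linear relation. A plot or a quadratic term would check that.

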#### Methods in analysis to handle protocol non-adherence and any statistical methods to handle missing data {20c}

Treatments with low adherence scores will still be included in the trial, but the level of adherence on the named scale will be included as a controlled variable on the level of the statistical analyses. For missing values, we will use classical methods of multiple imputations.

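### Hypothesis 3 compares mechanism change in responders and non-responders pooled over both arms with no arm term named, so an arm effect on both variables biases it modestly towards confirmation

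*Protocol article*

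**What the plan says.** All three relevant hypotheses stand in the protocol article under Objectives {7}:

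- Hypothesis 1: the 10-session treatment "produces more reduction in specific borderline symptoms than non-specific treatment as usual (TAU".
- Hypothesis 2: the same treatment "presents pre-post change in socio-cognitive processing (SCP) and emotion processing (EP), which is not the case in the TAU".
- Hypothesis 3: "SCP and EP change more in treatment responders, compared to non-responders (across conditions".

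Under Statistical methods {20a}, hypothesis 3 shares one sentence with hypothesis 2: "We will use multilevel modeling [103] where appropriate, for hypotheses 2 and 3 (global change and treatment response". Three controls are named that could apply to it. The first is therapist: "We will control for therapist effects in the three-level hierarchical linear modeling (HLM". The second is the fMRI data from the same assessment point. The third, in section {20c}, is adherence: "the level of adherence on the named scale will be included as a controlled variable". Neither section names treatment arm, or a comparison within arms, for hypothesis 3.

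**The concern.** By the plan's own predictions, arm drives both sides of the hypothesis 3 comparison: it raises the chance of being a responder (hypothesis 1) and the amount of mechanism change (hypothesis 2). Pooling the arms lets that shared dependence appear as an association between response and mechanism. Part of any pooled difference would then restate hypotheses 1 and 2 and say nothing about whether, among patients given the same treatment, those whose processes change more are those who improve.

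The direction matters as well as the size. When the treatment works, the bias always favours the hoped-for answer. The study sets out to explain symptom change, so a positive hypothesis 3 is likely to be read as support for the mechanisms. The primary outcome comparison is not affected.

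**Working it through.** **What the plan supplies.** It gives no figure for hypothesis 3, so there is nothing to reproduce. Its stated power of 0.819 does not bear on this point. From Sample size {14} I take N = 80, 30% dropout, so 80 × (1 − 0.30) = 56, two-sided alpha 0.05, and d = 0.60 as a scale for the arm effects.

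**What is assumed.** Allocation is 1:1 (Sequence generation {16a} gives two arms in blocks of 10 but no ratio). TAU response is 30%, varied from 20% to 40%. A responder is a patient beyond a fixed cut on normally distributed symptom change. The arm effect d is the same on symptom change and on mechanism change. There is no association between the two within either arm.

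**Closed form.** With no within-arm link, the pooled difference is

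difference = d × [P(GPM | responder) − P(GPM | non-responder)].

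For d = 0.60 and 30% response under TAU:

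1. GPM response = Φ(0.60 − 0.524) = Φ(0.076) = 0.530.
2. P(GPM | responder) = 0.530 / (0.530 + 0.300) = 0.639.
3. P(GPM | non-responder) = 0.470 / (0.470 + 0.700) = 0.402.
4. Difference = 0.60 × (0.639 − 0.402) = 0.142 SD.

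**Simulation.** 20,000 runs per setting, TAU response 30%. The pooled analysis is a t test; the adjusted analysis adds arm to a regression.

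| d on both variables | GPM response | Spurious difference (SD) | Pooled rejection, N = 56 | Pooled rejection, N = 80 | With arm in the model (N = 56 / 80) |
|---|---|---|---|---|---|
| 0 | 30.0% | 0.00 | 5.0% | 4.9% | 5.1% / 4.8% |
| 0.3 | 41.1% | 0.04 | 5.1% | 5.4% | 4.9% / 5.1% |
| 0.6 | 53.0% | 0.14 | 7.9% | 9.1% | 5.2% / 5.2% |
| 0.8 | 60.9% | 0.25 | 13.7% | 17.8% | 5.0% / 4.7% |
| 1.0 | 68.3% | 0.38 | 25.8% | 33.7% | 5.0% / 5.1% |

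The TAU response rate hardly matters. At d = 0.60, moving it from 20% to 40% gives a closed-form difference of 0.146 to 0.142 SD, with rejection of 7.7–8.1% (N = 56) and 8.8–9.4% (N = 80). A repeat simulation gave about 7.5% and 9.3%. With arm in the model, the spurious difference is zero to within 0.005 SD.

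**Do the named controls already remove it?** The protocol article gives 10 therapists for GPM (Sample size {14}) and 10 for TAU (Intervention description {11a}). Assume they are nested in arm, with N = 80, 30% response under TAU and 3,000 runs. A random therapist intercept without an arm term then gives:

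| d | Pooled, no therapist level | Random therapist level |
|---|---|---|
| 0.6 | 0.145 SD, 9.3% | 0.114 SD, 9.2% |
| 0.8 | 0.259 SD, 18.3% | 0.187 SD, 13.6% |
| 1.0 | 0.393 SD, 34.1% | 0.262 SD, 20.9% |

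The therapist level shrinks the bias but leaves much of it; at d = 0.6 the rejection rate barely moves. Therapists entered as fixed effects and nested in arm would remove it, but the plan describes a level of a hierarchical model. Adherence to GPM principles may track arm to some degree, but it is not an arm term, and the plan gives nothing from which to size its effect.

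**The case against.** The best reply is that Objectives {7} states a hypothesis and not a model. The phrase about conditions could mean that the relation holds whichever arm a patient is in, and an arm-adjusted model would test exactly that. Statistical methods {20a} only outlines the analysis, Trial design {8} calls the mechanisms part a controlled comparison, and a covariate list for a non-primary hypothesis often sits in a fuller document. This stands to the extent that an arm term is not excluded. It does not dispose of the point: the pooling is written into the hypothesis, controls are listed, and arm is not among them.

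Three stronger readings are tempting and not supported:

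- **That hypothesis 3 is worthless beside hypotheses 1 and 2.** At d = 0.60 the arm effect alone reaches significance in under 10% of trials, so it seldom confirms the hypothesis by itself. Hypothesis 4 tests mediation separately. As a plain description, the pooled difference in this scenario is real; it misleads only when read as a link between mechanism and response.
- **That the error rate is near 20%.** Response rates such as 20% and 60% give about 19% when the mechanism shift is 0.6 SD, but they imply a symptom effect of 0.84 + 0.25 = about 1.10 SD, well above the planned 0.60. The pilot's uncontrolled pre-post outcome effects were 0.41 to 0.51.
- **That splitting patients into responders and non-responders loses a known share of information.** Outcomes {12} says "The ZAN-BPD is a continuous hetero-administered measure", but the article does not state the responder rule, so no loss can be calculated. Keeping a responder contrast is a legitimate choice.

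**Conclusion.** The point holds in a limited form. Followed as written, hypothesis 3 is confounded by arm in the direction the trial hopes for. At the planning effect of 0.60 SD on both variables, the spurious difference is about 0.14–0.15 SD and the rejection rate about 7.5–9% against a nominal 5%. At 0.3 SD it is negligible; at 0.8 to 1.0 SD the rejection rate reaches roughly 14–34%.

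These figures rest on no within-arm association, equal arm effects on both variables, 1:1 allocation, TAU response of about 30%, and a final model without an arm term. If the final model contains arm, the problem disappears. The correction is worth making because it is nearly free and the bias is one-sided.

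**What to change.** State in {20a} that the hypothesis 3 model includes treatment arm, and report the responder versus non-responder difference in SCP and EP change within each arm. Say that only the arm-adjusted estimate will be interpreted as evidence linking mechanism to response; the pooled difference can stay as description. Clarify the bracketed phrase in hypothesis 3 so that it agrees with this. A supplementary analysis relating mechanism change to continuous, baseline-adjusted ZAN-BPD change, also with arm in the model, is optional.

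The cost is one degree of freedom and a responder difference that may be smaller than the pooled one. No new data are needed, and sample size and conduct do not change.
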